### **9.5 Interim Monitoring and Analyses**

Interim analyses of the accumulating data will be performed at regular intervals (at least annually) for review by the IDSMC. The IDSMC members will comply with a trial-specific IDSMC charter according to International Conference on Harmonisation Good Clinical Practice (ICH GCP) guidelines. These analyses will be performed at the MC-CTU by the trial statistician in accordance with the Standard Operating Procedures of the CTRC. The trial statistician at the MC-CTU will prepare the report for the IDSMC, the contents of which will be agreed by the IDSMC.

The data collected during the pilot phase will be used to check the estimate of the common standard deviation used in the sample size calculation of the full trial. The estimate obtained may be used to increase but not decrease the trial sample size. No formal comparisons of the trial primary outcome are planned at any interim analyses. If requested by the IDSMC the comparison will be made and the Peto-Haybittle stopping rule used to inform discussions.

The IDSMC will be asked to give advice on whether the accumulated data from the trial, together with results from other relevant trials, justifies continuing recruitment of further patients or further follow-up.

The full trial will open if the criteria listed in section 4.1 are met. A decision to discontinue recruitment, in all participants or in selected subgroups will be made only if the result is likely to convince a broad range of clinicians including participants in the trial and the general clinical community. If a decision is made to continue, the IDSMC will advise on the frequency of future reviews of the data on the basis of accrual and event rates. The IDSMC will make recommendations to the TSC (TSC, see section 16) as to the continuation of the trial.

## **9.6 Analysis Plan**

The trial will be analysed and reported using the 'Consolidated Standard of Reporting Trials' (CONSORT) and the International Conference on Harmonisation E9 guidelines. A full and detailed statistical analysis plan will be developed prior any comparative analysis of the trial data. The main features of the statistical analysis plan are included here.

A p-value of 0.05 or less will be used to declare statistical significance for all analyses. Rather than adjust for multiplicity relevant results from other studies already reported in the literature will be taken into account in the interpretation of results.

Primary analysis will be the intention to treat principle, a secondary analysis will be conducted using the per protocol approach. The purpose of the per protocol approach is to consider the robustness of the conclusions reached from the analysis using the intention to treat principle to protocol deviations.

The primary outcome HbA1c will be compared between the trial groups using a two group t-test. Difference in means with 95% confidence intervals will be presented. Analysis of covariance will be used to adjust for baseline values (excluding HbA1c measured at baseline) and important prognostic factors.

Missing data will be monitored and strategies developed to minimise its occurrence, however as much data as possible will be collected about the reasons for missing data and this will be used to inform the handling of missing data.

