### 4.1 Pilot Study

An inbuilt pilot study (n=30) will test the feasibility of recruitment to this study protocol. The full study (n=316) will open if the following criteria are met:

- a. Fifty percent or more patients who are eligible and are invited to participate in the pilot study are successfully recruited;
- b. Demographic characteristics like age, ethnicity, gender and deprivation score are not considered to be significantly different in the group of patients who are recruited compared to those who decline. These characteristics are significantly associated with glycaemic control (24-26)

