### **9.2 Method of Randomisation**

Participants will be remotely randomised in a 1:1 ratio using a web service. The randomisation code list will be generated by a statistician using block randomisation with random variable block size method at the MC-CTU. Participants will be randomised to either MDI or CSII treatment in a ratio of 1:1 and will be stratified by centre and age.

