#### **Full Trial**

A sample size of 143 in each group will have 80% power to detect a difference in means of 0.50 assuming that the common standard deviation is 1.50 using a two group t-test with a 0.05 two-sided significance level. Allowing for 10% loss to follow up means we would need a total of 316 participants (158 per group). The estimate used for the standard deviation in the sample size calculation was taken from an audit at Alder Hey Children's NHS Foundation Trust based on children matching the inclusion criteria for this proposed study. A difference in HbA1c of 0.5% is widely recognized as the threshold used by the Food and Drug Administration (FDA) and pharmaceutical industry to determine effectiveness of any new oral hypoglycaemic agents. Current national studies investigating therapeutic interventions in children with diabetes were powered using this effect size. An improvement of 0.61% was detected in adults in the meta-analysis of studies included in the 2004 HTA report suggesting that in addition to this estimate being the minimum clinically important it is also a realistic difference to detect.

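### The named primary test ignores the stratification factors centre and age, and the protocol does not say whether the t-test or the planned ANCOVA is primary

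*Protocol*

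**What the plan says.** - **Primary test.** Section 9.6 states: "The primary outcome HbA1c will be compared between the trial groups using a two group t-test". The difference in means is to be given with a 95% confidence interval.
- **Adjusted analysis.** The same paragraph adds: "Analysis of covariance will be used to adjust for baseline values (excluding HbA1c measured at baseline) and important prognostic factors". It lists no covariates and does not say whether this analysis or the t-test decides the primary question.
- **Randomisation.** Section 9.2 uses "block randomisation with random variable block size method" with 1:1 allocation, and participants "will be stratified by centre and age".
- **Prognostic value.** Section 4.1 lists age, ethnicity, gender and deprivation score and says: "These characteristics are significantly associated with glycaemic control". It gives no effect size and says nothing of the kind about centre.
- **Sample size.** Section 9.4 states: "A sample size of 143 in each group will have 80% power" for a difference of 0.50 with SD 1.50, "using a two group t-test with a 0.05 two-sided significance level". The total is 316 after allowing for 10% loss.

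**The concern.** Blocked randomisation within centre and age strata largely removes differences between strata from the treatment contrast. A two-group t-test does not take this into account. Its standard error is built from the total variance, which still contains the differences between centres and between age groups. If those differences are real, the test reports more uncertainty than the design leaves. The interval is then too wide and the test rejects a true null less often than 5%.

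The unstated rank of the ANCOVA is part of the same problem. Section 9.6 applies a 0.05 threshold to all analyses without multiplicity adjustment. If the t-test and the ANCOVA fell on opposite sides of 0.05, the protocol does not say which of them answers the primary question.

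**Working it through.** **Inputs from the protocol.** Difference 0.50, common SD 1.50, two-sided 0.05, 80% power, 143 per group analysed, 158 per group randomised (9.4); blocked randomisation stratified by centre and age, 1:1 (9.2).

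**Inputs that are assumed.** The share of 12-month HbA1c variance explained by centre and age together (R²), taken as 0 to 0.20. For the simulation: 15 centres, 2 age bands, blocks of 2 or 4, and the explained variance split equally between centre and age. The protocol gives none of these.

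**Step 1: reproduce the plan.** The standardised difference is 0.50/1.50 = 0.333. The t-based calculation gives 142.25, so 143 per group with 80.2% power. The stated 143 reproduces. The stated total follows from 143 × 1.1 = 157.3, so 158 per group and 316. If 10% of 158 are lost, 142.2 per group remain and power is 80.0%.

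**Step 2: the standard error that the t-test reports.** 1.5 × √(2/143) = 0.177, whatever R² is.

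**Step 3: the true standard error.** If blocking balanced the strata perfectly, it would be 0.177 × √(1 − R²). Incomplete blocks in small strata leave it somewhat higher.

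**Step 4: type I error of the t-test.** In the perfectly balanced limit this is 2 × [1 − Φ(1.96/√(1 − R²))].

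**Step 5: power of the adjusted analysis.** The residual SD is 1.5 × √(1 − R²), put into the t-based power formula with 143 per group.

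The simulation used 3,000 runs per setting with 286 analysed. It compared the t-test with a linear model containing centre and age indicators.

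| Assumed R² | True SE, limit | True SE, simulated | t-test type I error, limit | t-test type I error, simulated | t-test power, simulated | Adjusted power, formula | Adjusted power, simulated |
|---|---|---|---|---|---|---|---|
| 0 | 0.177 | 0.179–0.181 | 5.0% | 5.4% | 79.8% | 80.2% | 79.4% |
| 0.05 | 0.173 | 0.174–0.176 | 4.4% | 5.2% | 80.9% | 82.2% | 82.1% |
| 0.10 | 0.168 | 0.170–0.172 | 3.9% | 4.5% | 80.9% | 84.2% | 84.3% |
| 0.20 | 0.159 | 0.160–0.162 | 2.8% | 3.2% | 83.0% | 88.1% | 88.0% |

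Monte Carlo error is about √(0.05 × 0.95/3000) = 0.4 points for type I error and √(0.8 × 0.2/3000) = 0.7 points for power. The simulated 5.2% at R² = 0.05 therefore cannot be told apart from 5%. The fall below 5% is clear only at the larger R².

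**Step 6: power forgone (simulated adjusted minus simulated t-test).** None at R² = 0; 82.1 − 80.9 = 1.2 points at 0.05 (2.0 if the formula value 82.2% is set against the design value 80.2%); 84.3 − 80.9 = 3.4 at 0.10; 88.0 − 83.0 = 5.0 at 0.20.

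**The case against.** **An adjusted analysis is already planned.** This is true, and a reader who sees only the t-test sentence might infer that none exists. The ANCOVA stands in the same paragraph, and age would fit its description of prognostic factors in the light of section 4.1. What remains is that neither stratification factor is named and the ANCOVA's standing against the t-test is open.

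**Covariate lists belong in the SAP.** Largely fair: the full list can wait. But the protocol does not leave the primary test open. It presents section 9.6 as the main features of the plan and names the test there. The choice of an unstratified test is therefore one that the protocol itself makes.

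**The trial is not underpowered.** Correct. A reader might infer that ignoring the strata takes power below 80%. It does not: 143 per group was derived for this same unadjusted test using the total SD, and the simulated power of the t-test stays at about 80% or above.

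**The error is in the safe direction.** Also correct. The unadjusted contrast is unbiased under randomisation, and the t-test raises no false-positive risk.

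**The size rests on assumed inputs.** This stands in full. No variance share, number of centres or age banding is given, and nothing in the protocol says that centre is prognostic.

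**Conclusion.** The point holds as one of efficiency and clarity. The protocol fixes an unadjusted t-test after stratifying by centre and age, and does not say how the ANCOVA ranks against it. So far as those factors predict HbA1c, the t-test is conservative. At an assumed R² of 0.20, for example, it reports a standard error of 0.177 against a true value of about 0.16, with type I error of about 3%. The planned power is met. The cost is extra power forgone: none at R² = 0, about 1 to 2 points at 0.05, about 3 at 0.10 and about 5 at 0.20. The direction follows from the design together with the statement about age in section 4.1. The size is conditional on R² values that are assumptions. The documents do not support a claim that the trial falls short of its design power, that the primary result would be biased, or that centre is known to matter.

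**What to change.** In section 9.6, and in the SAP to match, state that the single primary analysis is a linear model of 12-month HbA1c on allocated arm, adjusted for the age stratum used at randomisation and for centre. Fit centre as a random effect, or pool small centres by a rule set in advance, since the number of centres is not given. Report the adjusted mean difference with its 95% confidence interval. Keep the unadjusted t-test as a supportive analysis.

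The cost is a few sentences of wording before any comparative analysis. Both factors are already recorded for randomisation, so no new data are needed. The sample size can stay as it is, because it was set for the less efficient test.

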### 8.2.1 HbA1c

A glycosylated haemoglobin (HbA1c) level indicates the mean concentration of glucose in the participant's body over the preceding three month period. A blood sample (finger prick; approximately 3 drops) from all the participants will be collected at each site by the diabetes clinical care team for the analysis of HbA1c (as primary end point of the trial) prior to start of the randomised treatment then at 3, 6, 9 and 12 months.

The blood sample will be collected and analysed in line with local hospital laboratory standards.

Additionally, a blood sample will be collected in a tube identified by initials, study unique number and date/time of sample. The sample will be sent securely to a central clinical pathology laboratory at Alder Hey Children's NHS Foundation Trust for analysis to check standardisation of results from local hospital laboratories.

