## **9.7 Economic analysis**

The primary economic analysis will be based on an assessment of the incremental costs per QALY gained. Additionally, a cost-consequences analysis will be performed based on the primary and secondary outcome measures. Costs and benefits will be discounted at an annual rate of 3.5% (36).

ICERs will be estimated, with uncertainty in parameter estimates being addressed through the application of bootstrapping and the estimation of cost-effectiveness acceptability curves (38). A regression analysis of cost and QALYs, with age, baseline HbA1c, utility (39) and other covariates as deemed appropriate, will be conducted to conserve any correlation between costs and benefits, and minimise bias in the cost utility estimate. Estimates of ICERs will be compared with the £20,000 to £30,000 per QALY threshold of cost-effectiveness set by NICE (1), and a range of univariate and probabilistic sensitivity analyses will be conducted to assess the robustness of the analysis. Additionally, trial results will be extrapolated to estimate lifetime costs and benefits to avoid time horizon selection bias, and to capture long-term micro- and macrovascular complications. We will approach IMS Health for permission to use the CORE diabetes model (40) and parameterise with estimates derived from the trial.

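### Section 9.6 bars baseline HbA1c from the covariance analysis of 12-month HbA1c without giving a reason; this forgoes a probably modest gain in precision in the adjusted analysis, at almost no saving

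*Protocol*

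**What the plan says.** Section 9.6 of the protocol makes an unadjusted two-group t-test the comparison for the primary outcome, HbA1c at 12 months. It then adds an adjusted analysis: "Analysis of covariance will be used to adjust for baseline values (excluding HbA1c measured at baseline) and important prognostic factors". The amendment log for version 4.0 (section 18.3) records the exclusion as a clarification, so it is deliberate. Neither place explains it.

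Four other passages bear on the choice.

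- Section 8.2.1 plans an HbA1c sample for all participants "prior to start of the randomised treatment then at 3, 6, 9 and 12 months", and section 6.3 requires baseline assessments to be complete before randomisation.
- Section 9.2 allocates "in a ratio of 1:1 and will be stratified by centre and age". HbA1c is not a stratification factor.
- Section 9.7 plans a regression of costs and QALYs "with age, baseline HbA1c, utility (39) and other covariates as deemed appropriate".
- Section 9.4 sizes the full trial on an unadjusted comparison: "A sample size of 143 in each group will have 80% power to detect a difference in means of 0.50". The SD behind this figure is 1.50, and the test is a t-test, two-sided at the 5% level.

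**The concern.** The pre-treatment value of the outcome is usually the first candidate for a covariance model. Here the model admits other baseline values and prognostic factors and names this one for removal. A variable fixed before randomisation cannot bias a randomised contrast when it is adjusted for, and it uses one degree of freedom. Possible weak prognostic value is a reason to expect little gain, not a reason to prohibit the covariate.

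Two things are at stake. The adjusted analysis is less precise than it could be. It is also the analysis to which a reader would turn if the arms differed at baseline, and as written it cannot deal with an imbalance in presenting HbA1c. If one appeared, adding the covariate afterwards would contradict the protocol and look data-driven.

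**Working it through.** **Inputs from the protocol.** Difference 0.50 and common SD 1.50 (HbA1c, %), two-sided 0.05, 80% power, 143 per group, 316 in total with a 10% loss allowance (section 9.4); 1:1 allocation (section 9.2).

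**Input not in the protocol.** The correlation r between baseline and 12-month HbA1c. It is assumed and shown as a range.

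**Step 1: reproduce the stated sample size.** The normal approximation gives 142 per group. The exact two-group t-test (noncentral t) gives 79.9% power at 142 and 80.2% at 143, so 143 is right. For the total, 143 × 1.1 = 157.3, rounded up to 158 per group, or 316. Dividing by 0.9 instead gives 159 per group, or 318, two children more. The calculation uses the unadjusted SD, so it does not rely on baseline adjustment and the exclusion does not make it wrong.

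**Step 2: effect of adjusting on precision.** Residual SD = 1.5 × √(1 − r²), and the variance falls by r². The half-width of the 95% interval is 1.96 × residual SD × √(2/143). Power is recalculated by the same t-test with the residual SD; the one lost degree of freedom out of 284 is ignored.

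**Step 3: effect of a chance imbalance on the unadjusted difference.** At 143 per group, the standard error of a baseline difference, in baseline SD units, is √(2/143) = 0.118. A difference of 1.96 standard errors is 0.232 SD. It moves the unadjusted 12-month difference by r × 0.232 × 1.5.

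| Assumed r | Variance reduction | Residual SD | 95% CI half-width | Power at 143 per group | n per group for 80% | Shift from a 1.96-SE imbalance |
|---|---|---|---|---|---|---|
| 0 (no gain) | 0% | 1.500 | 0.348 | 80.2% | 143 | 0 |
| 0.1 | 1% | 1.492 | 0.346 | 80.6% | 141 | 0.035 |
| 0.2 | 4% | 1.470 | 0.341 | 81.8% | 137 | 0.070 |
| 0.3 | 9% | 1.431 | 0.332 | 83.8% | 130 | 0.104 |
| 0.5 | 25% | 1.299 | 0.301 | 90.0% | 107 | 0.174 |

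The row for 0.5 only shows how steeply the gain rises with r; nothing in the protocol supports a value that high.

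**Step 4: how large r is likely to be.** Section 8.2.1 says that HbA1c reflects glucose over the previous three months. Sections 5.1 and 5.2 admit only newly diagnosed children not treated before for diabetes. The baseline value therefore mostly describes hyperglycaemia before diagnosis, not control under treatment. A weak correlation is plausible, which points to the upper rows of the table.

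**The case against.** The strongest reply is that this is a deliberate and defensible choice with little consequence. Its parts fare differently.

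- *The primary comparison has no covariates.* This stands. A reader might infer that the exclusion leaves a chance imbalance in the primary estimate. But that estimate comes from the t-test, and deleting the parenthesis alone would not change it. The t-test's standard error already allows for chance imbalance, so its type I error and interval coverage hold.
- *Baseline HbA1c at diagnosis is not an ordinary baseline.* This stands as a reason to expect a small gain. A reader might infer from the exclusion that substantial precision is thrown away. The protocol gives no correlation, and at 0.1 to 0.2 power rises by only 0.4 to 1.6 percentage points.
- *Sections 9.6 and 9.7 do not conflict.* This largely stands. A reader might see a contradiction, but section 9.7 models costs and QALYs for its own stated purposes, and different outcomes may have different predictors. What remains is that the protocol treats the same measurement as a useful covariate in one analysis and bars it from the other, without explanation.
- *The detail belongs in the analysis plan.* This does not answer the point. The protocol has not left the matter open: it fixes a rule, and an analysis plan that follows the protocol would inherit it.
- *Sampling of all participants is a plan, not a guarantee of complete data.* True, and the fix has to allow for missing baseline values.

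**Conclusion.** The point holds as one about efficiency and robustness in the adjusted analysis. The exclusion is explicit and unexplained, and it removes a pre-treatment covariate that is to be collected anyway. It introduces no bias, does not inflate the type I error, and leaves the sample size of 143 per group intact.

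If r lies between 0.1 and 0.3, admitting the covariate would cut the variance by 1% to 9% and raise power from 80.2% to between 80.6% and 83.8%. It would also remove a shift of up to 0.035 to 0.10 HbA1c points for an imbalance of 1.96 standard errors, against a target difference of 0.50. These figures rest on the assumed correlation, on the planned SD of 1.50, and on 143 evaluable children per group with baseline values. The improvement is probably small, and it is worth making because it costs so little.

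**What to change.** In section 9.6, delete the parenthesis that excludes baseline HbA1c. Prespecify baseline HbA1c as a covariate in the covariance analysis, together with age stratum and centre, the two stratification factors of section 9.2. Keep the model without baseline HbA1c as a sensitivity analysis, and carry the same wording into the statistical analysis plan.

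Decide separately whether this model or the unadjusted t-test is the primary comparison, and say so. The gain reaches the primary estimate only if the covariance model is named as primary. That is a larger change than deleting the parenthesis.

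If the sponsor prefers to keep the exclusion, the least that should be done is to state the reason and to prespecify a sensitivity analysis that includes baseline HbA1c.

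The cost is the wording, one degree of freedom, and a simple prespecified rule for missing baseline values, such as substituting the overall baseline mean or using a missing-value indicator. No new data, visits or participants are needed.

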## **9.7 Economic analysis**

The primary economic analysis will be based on an assessment of the incremental costs per QALY gained. Additionally, a cost-consequences analysis will be performed based on the primary and secondary outcome measures. Costs and benefits will be discounted at an annual rate of 3.5% (36).

ICERs will be estimated, with uncertainty in parameter estimates being addressed through the application of bootstrapping and the estimation of cost-effectiveness acceptability curves (38). A regression analysis of cost and QALYs, with age, baseline HbA1c, utility (39) and other covariates as deemed appropriate, will be conducted to conserve any correlation between costs and benefits, and minimise bias in the cost utility estimate. Estimates of ICERs will be compared with the £20,000 to £30,000 per QALY threshold of cost-effectiveness set by NICE (1), and a range of univariate and probabilistic sensitivity analyses will be conducted to assess the robustness of the analysis. Additionally, trial results will be extrapolated to estimate lifetime costs and benefits to avoid time horizon selection bias, and to capture long-term micro- and macrovascular complications. We will approach IMS Health for permission to use the CORE diabetes model (40) and parameterise with estimates derived from the trial.

